#### Cost analysis

To compare costs between the two groups, confidence intervals for the difference in mean costs are calculated using bias-corrected and accelerated bootstrapping with 2000 replications [38].

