## Methods

### Design

A cluster randomized controlled clinical trial is carried out among five intervention homes and five usual care homes for the elderly in the north-west of the Netherlands that comprise over five hundred residents. There is a follow up of six months (Figure 1). The ethical committee of the VU medical center approved the study.

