### Randomization

The randomization is carried out on home matched by percentage of psycho geriatric (i.e. cognitive impaired) residents. The care services and type of disability in homes with a high percentage of psycho geriatric patients are likely to differ depending on how many residents need psycho geriatric care. So, the homes were first ranked on percentage of psycho geriatric patients. The two homes with the highest percentage of psycho geriatric patients were than matched, and so on.

Next, we checked the risk of imbalance in numbers following Pocock's recommendations [23]. If the difference in number of intervention and control residents would be >15% (75 or more) the randomization should be repeated until the imbalance was 15% or less.

Homes were all ordered on the percentage psycho-geriatric patients and numbered from rank one to rank 10. In this way matched homes are ranked after each other, one having an even and the other an uneven number. Randomization was carried out using Pocock's first column in his random numbers table [23]. If the table's first number is even, the even number of first matched home is assigned the intervention. If the next table number is uneven, the uneven number of the next matched couple is assigned the intervention. And so on until all matched couples are assigned.

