### Sample size calculation

Sample size calculations are based on the expected effects of the intervention on the main outcome measures concerning quality of care and functional health. In the following sample size calculations we used an alpha of 0.05, power of 80% and inflation of 10% because of anticipated intra-cluster correlation in the homes for the elderly. Regarding health related quality of life, Cohen's D effect size ranged from 0.5 to 3.8 in our meta-analysis [22]. To detect a fair benefit, i.e. effect size = 0.5, a minimum of 64 persons is needed in each group [35]. For functional health and disability we anticipate on a comparable effect-size and consequently identical sample size. Furthermore if we assume a dropout rate of 15% during the 6 months follow-up we need to include at least 100/85 × 64 × 110% = 82 persons in each group.

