#### Cost effectiveness analysis

For the cost-effectiveness analysis the difference in total costs between the intervention and usual care group are compared with the difference over 6 months in improvement of functional health and disability. In addition, a cost utility analysis will be done to assess the incremental costs per Quality Adjusted Life Years (QALY). QALY's are calculated by multiplying the utility based on EuroQol scores [29] with the amount of time a patient spent in this particular health state. Transitions between health states are linearly interpolated.

Uncertainty around the cost-effectiveness and cost-utility ratios is calculated using the bias-corrected percentile method (5000 replications) and presented in a cost-effectiveness plan [39]. The bootstrapped cost and effect pairs will also be used to calculate cost-effectiveness acceptability curves [40].

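### The cost and cost-effectiveness bootstraps take no account of the ten randomised homes; if residents are resampled as independent, the economic uncertainty is understated by an amount the article does not allow to be fixed

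*Protocol article*

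**What the plan says.** The Design section of the protocol article states: "A cluster randomized controlled clinical trial is carried out among five intervention homes and five usual care homes for the elderly", in homes "that comprise over five hundred residents". Under Randomization, "The randomization is carried out on home matched by percentage of psycho geriatric" residents, which gives five matched pairs. The Sample size calculation section uses "an alpha of 0.05, power of 80% and inflation of 10% because of anticipated intra-cluster correlation in the homes for the elderly".

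Two bootstraps are then fixed for the economic evaluation:

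- Cost analysis: "confidence intervals for the difference in mean costs are calculated using bias-corrected and accelerated bootstrapping with 2000 replications".
- Cost effectiveness analysis: "Uncertainty around the cost-effectiveness and cost-utility ratios is calculated using the bias-corrected percentile method (5000 replications" being the number given there). The same cost-effect pairs supply the cost-effectiveness plane and the acceptability curves.

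Neither section mentions homes, matched pairs, a two-stage scheme or a multilevel model. The Data analysis section speaks only of univariable and multivariable comparisons between the groups, so it supplies no clustering method that the economic sections could borrow.

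**The concern.** A bootstrap reproduces the sampling variation of the unit it resamples. If residents are drawn as independent, the variation between homes that reaches the arm means is mostly lost, although it is part of the uncertainty when only five homes stand in each arm. Bias correction and acceleration adjust for bias and skewness. They do not restore between-home variance, and more replications do not help.

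The article expects such variance: it inflates the sample size for intra-cluster correlation, and its Discussion accepts that the culture of individual homes will not balance out between arms. Economic effects are part of the stated objective and QALYs are a primary outcome. The cost difference, the cost per QALY and the probability of being cost-effective would all carry the same understatement.

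**Working it through.** **Inputs from the article.** 5 homes per arm; over 500 residents; 64 per group before inflation ("effect size = 0.5, a minimum of 64 persons is needed in each group"); 10% inflation for clustering; 15% dropout ("if we assume a dropout rate of 15% during the 6 months follow-up"). **Not given, so assumed:** any ICC for costs or QALYs.

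**The article's own figure.** A two-sided t-test with effect size 0.5, alpha 0.05 and power 80% needs 63.8, so 64 per group. Then 64 × 1.10 / 0.85 = 82.8, stated as 82. It reproduces, apart from rounding down.

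**Residents per home.** The stated minimum gives 82 / 5 = 16.4. Taking 500 residents less 15% dropout gives 500 × 0.85 / 10 = 42.5; this assumes that all 500 take part.

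**Formulas.** Design effect DE = 1 + (m − 1) × ICC, with m residents per home. A resident-level standard error (SE) is too small by the factor √DE. Coverage of a nominal 95% interval is then about 2Φ(1.96/√DE) − 1. This takes equal home sizes and no gain from matching.

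**ICC implied by the 10% inflation.** At 16.4 per home: 0.10 / 15.4 = 0.0065. At 42.5 per home: 0.10 / 41.5 = 0.0024.

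| Assumption | DE | SE factor | Coverage |
|---|---|---|---|
| Article's own inflation | 1.10 | 1.05 | 94% |
| ICC 0.0065, 42.5 per home | 1 + 41.5 × 0.0065 = 1.27 | 1.13 | 92% |
| ICC 0.05, 42.5 per home | 1 + 41.5 × 0.05 = 3.08 | 1.75 | 74% |

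The second row carries an ICC derived at one home size to another. That is appropriate because an ICC, unlike a design effect, does not change with the number of residents per home.

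**Check with the named method.** The formula is a normal approximation, so the bias-corrected and accelerated bootstrap of residents with 2000 replications was also simulated: skewed (gamma) costs, a normal home effect, 5 homes of 50 per arm, no matching effect, 600 runs per setting. Two home-level alternatives were run on the same data.

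| ICC | Residents resampled | Whole homes resampled, percentile | Home means, t on 8 df |
|---|---|---|---|
| 0 | 94% | 89% | 95% |
| 0.01 | 88% | 89% | 96% |
| 0.02 | 83% | 88% | 96% |
| 0.05 | 72% | 88% | 96% |
| 0.10 | 57% | 87% | 94% |

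With 16 per home, the resident-level interval covered 92%, 92%, 89%, 84% and 75% at the same ICCs. At 50 per home, coverage is close to nominal at ICC 0, so the loss further down comes from clustering and not from skewness. At 16 per home, about 3 points are already lost at ICC 0.

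Resampling whole homes undercovers at every ICC because five homes per arm are too few for a percentile interval.

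**The case against.** **The resampling unit is not stated.** This is a condensed article, and such detail is often left to an analysis plan. A reader might infer that the article prescribes independent resampling of residents. It does not say so, and that part of the objection stands. Silence alone would not be a finding. But the article goes as far as fixing the interval type and the replication count for both economic analyses, and leaves out the one choice that decides validity in a cluster trial. Nothing elsewhere in it fills the gap, and an analyst following the text would most naturally run an ordinary bootstrap.

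**The size depends on an assumed ICC.** This also stands. A reader might infer from the ICC 0.05 row that the economic results would look far more certain than the design allows. The documents do not support that: their only clustering figure is the 10% inflation, at which the error is about 5% on the SE. Whether 10% is adequate is a separate question about the sample size.

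**Matching may recover some between-home variance.** It may, and the tables ignore it. The bootstraps as described do not use it either.

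**The ratio interval.** A reader might add that an interval for a ratio has no clear meaning once replicates fall in several quadrants of the plane. The article gives no figures to show that they will, and it already plans the plane and acceptability curves, which display such spread. This is a reporting preference and not part of the point.

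**Conclusion.** The point holds conditionally. The economic bootstraps are specified without the randomised homes or their pairs. If residents are resampled as independent, every economic interval, the plane and the acceptability curves understate uncertainty for any positive ICC. The direction is certain under that reading; the size is not. It runs from an SE factor of about 1.05 at the article's own design effect, through about 1.13 when its implied ICC is applied to the larger homes, to about 1.75 at an assumed ICC of 0.05. The first two are modest. The third would matter, but it rests on an ICC that the article neither gives nor implies. This is worth correcting before the cost data are analysed. It does not show that the economic conclusions would be wrong.

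**What to change.** In the Cost analysis and Cost effectiveness analysis sections, or in the analysis plan behind them, replace the ordinary bootstrap with a named method that respects homes and, where feasible, matched pairs, handles costs and effects jointly, and suits five homes per arm. Any of these would serve:

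- a two-stage bootstrap (homes, then residents within homes) with shrinkage correction;
- a bivariate mixed model for costs and effects with a home random effect and small-sample degrees of freedom;
- a home-level analysis with t-based intervals.

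Of these, only the home-level t interval was simulated here (94% to 96% coverage). A plain percentile bootstrap of whole homes should not be chosen, since it reached only 87% to 89%. The plan should also say whether pairs enter the analysis: five pairs leave 4 degrees of freedom (5 − 1), against 8 (10 − 2) for unpaired home means, so using them is a trade-off to settle in advance.

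Build the cost-effectiveness plane and the acceptability curves from the same cluster-aware analysis. Reporting incremental net benefit is optional.

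The cost is revised wording, some programming and wider intervals. No new data are needed.

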#### Cost effectiveness analysis

For the cost-effectiveness analysis the difference in total costs between the intervention and usual care group are compared with the difference over 6 months in improvement of functional health and disability. In addition, a cost utility analysis will be done to assess the incremental costs per Quality Adjusted Life Years (QALY). QALY's are calculated by multiplying the utility based on EuroQol scores [29] with the amount of time a patient spent in this particular health state. Transitions between health states are linearly interpolated.

Uncertainty around the cost-effectiveness and cost-utility ratios is calculated using the bias-corrected percentile method (5000 replications) and presented in a cost-effectiveness plan [39]. The bootstrapped cost and effect pairs will also be used to calculate cost-effectiveness acceptability curves [40].

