### Data analysis

Effect analyses will be performed both on 'intention to treat' and per protocol principles. Differences between intervention and usual care patients at 6 months on the outcome measures (risk adjusted interRAI LTCF based Quality indicators, EuroQoL, functional health and disability) will be compared between the intervention and control group by both univariate and multivariate techniques. We will use the multivariate technique to adjust for possible differences in baseline scores and background variables between the intervention and control groups. Dropout and loss to follow up will be described. Potential effect-modification will be explored.

Especially, possible differential effects of disease management will be explored across residents with complex and simple health problems.

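### The cost-effectiveness ratio uses a difference in improvement for functional health and disability, while the effect analysis uses the 6-month difference with and without baseline adjustment, so the two need not agree

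*Protocol article*

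**What the plan says.** **Protocol article, Data analysis.** The effect is stated as "Differences between intervention and usual care patients at 6 months on the outcome measures", and functional health and disability are among the measures listed. The arms are compared "by both univariate and multivariate techniques". On the second of these the section adds: "We will use the multivariate technique to adjust for possible differences in baseline scores and background variables between the intervention and control groups". Neither analysis is named as the main one.

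**Protocol article, Cost effectiveness analysis.** For the same outcomes, the cost difference is "compared with the difference over 6 months in improvement of functional health and disability". No covariate is mentioned. Bootstrapped pairs of cost and effect then feed the cost-effectiveness plane and the acceptability curves.

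**Related facts.** The Design section gives five intervention and five usual care homes with over 500 residents. The Randomization section matches homes on the percentage of psychogeriatric residents only. Table 1 collects functional health and disability at baseline and at 6 months.

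**The concern.** Improvement over 6 months is, on its plain reading, the 6-month score minus the baseline score. A difference in mean improvement subtracts the whole baseline imbalance between the arms. The univariate 6-month comparison subtracts none of it, and the multivariate comparison subtracts a fraction estimated from the data. The three estimates coincide only if the arms are balanced at baseline.

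With ten homes that balance cannot be counted on. Matching on psychogeriatric share may help somewhat, but function is not a matching factor. The Data analysis section itself provides for baseline differences, and the Discussion accepts that features of individual homes may be spread unevenly over the arms.

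At stake is the consistency of the economic and clinical results. A reader could find one effect on functional health in the outcome table and another in the denominator of the ratio, with no stated reason for the gap.

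**Working it through.** **1. The plan's own figure.** The Sample size calculation section states "effect size = 0.5, a minimum of 64 persons is needed in each group". With two-sided alpha 0.05 and 80% power, a t-test needs 63.8, so 64. With 10% inflation and 15% dropout, 100/85 × 64 × 1.10 = 82.8, against 82 stated. The point does not depend on these numbers; the effect size of 0.5 serves only as a yardstick.

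**2. How the estimates relate.** Let D0 and D6 be the arm differences at baseline and at 6 months, and b the slope on baseline.
- univariate: D6
- adjusted: D6 - b·D0
- improvement: D6 - D0

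Improvement differs from univariate by D0, and from adjusted by (1 - b)·D0.

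**3. Plausible size of D0.** Assumptions, none given in the article except that 50 per home fits ten homes and over 500 residents: m = 50 per home, ICC = 0.05, no gain from matching.

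SD of D0 = sqrt(ICC + (1 - ICC)/m) × sqrt(2/5) = sqrt(0.05 + 0.019) × 0.632 = 0.263 × 0.632 = 0.166 SD.

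For ICC 0.01 and 0.10 it is 0.109 and 0.217 SD.

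**4. Gap to the adjusted estimate.** Assume a baseline to 6-month correlation r = 0.6 and equal SDs, so b is about 0.6.
- Typical (one SD): 0.4 × 0.166 = 0.066 SD, or 13% of 0.5.
- 95% range: 1.96 × 0.066 = 0.13 SD, or 26% of 0.5.
- Typical gap for ICC 0.01 to 0.10: 0.044 to 0.087 SD.
- Typical gap at ICC 0.05 for r = 0.3 and 0.9: 0.7 × 0.166 = 0.12 SD and 0.1 × 0.166 = 0.02 SD.

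The typical gap to the univariate estimate is the full 0.17 SD.

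**5. Precision, independent residents.** Variance of change over adjusted = 2(1 - r)/(1 - r²) = 2/(1 + r): 1.33, 1.25 and 1.18 at r = 0.5, 0.6 and 0.7. Against the univariate difference the ratio is 2(1 - r), which is 0.80 at r = 0.6, so there the change score is the more precise.

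**6. Precision, clustered.** Let h be the correlation over time of true home effects and w that within homes, with w = (r - ICC·h)/(1 - ICC). Variance of a home mean:
- change: 2·ICC(1 - h) + 2(1 - ICC)(1 - w)/m
- adjusted: ICC(1 + b² - 2bh) + (1 - ICC)(1 + b² - 2bw)/m

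With r = b = 0.6, ICC = 0.05, m = 50 and h = 0.9, w = (0.6 - 0.045)/0.95 = 0.584. Change: 0.0100 + 0.0158 = 0.0258. Adjusted: 0.0140 + 0.0125 = 0.0265. Ratio 0.97.

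| h | change / adjusted variance |
|---|---|
| 0.6 | 1.25 |
| 0.8 | 1.10 |
| 0.9 | 0.97 |
| 1.0 | 0.78 |

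The direction turns on h, which the article does not give.

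**The case against.** **The economic section does not say the change score is unadjusted.** True. If improvement is regressed on arm and baseline, the arm effect is identical to that from regressing the 6-month score on arm and baseline; in one simulated data set with 64 per group both gave 0.4023, against 0.3845 for raw change and 0.4192 for the raw 6-month difference. So the two sections could be reconciled. But the economic section states no such model, and its plain wording is a difference in improvement.

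**This is detail that a condensed article may leave to a fuller plan.** That is fair for the mechanics inside each bootstrap replicate. It does not cover the effect measure, which the article states in both places and words differently.

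**There is no single clinical effect for the ratio to contradict.** This stands in part. The effect analysis is both univariate and multivariate, so the adjusted difference is not the trial's only reported effect. The raw improvement still matches neither of the two when baseline is unbalanced.

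**A reader might infer that the ratio rests on a biased or generally less precise effect.** The documents do not support that. Under randomisation all three estimators have the same expected mean difference; a gap tied to the realised imbalance is conditional, and over randomisations it is not bias. The 18% to 33% excess variance holds for independent residents, or for homes no more stable over time than their residents. At ICC 0.05 and 50 per home, about 72% of the variance of a home mean lies between homes (0.05/0.069). If home differences persist strongly, the change score can be the more precise.

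**Conclusion.** The point holds as an inconsistency in the stated effect measure, and it is minor. For the same two outcomes the effect analysis uses 6-month differences, with and without baseline adjustment, and the cost-effectiveness ratio uses what reads as an unadjusted difference in improvement. Unless the arms are balanced at baseline, the effect in the ratio will equal neither.

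The typical gap to the adjusted estimate is about 0.07 SD. That figure rests on an assumed correlation of 0.6, ICC of 0.05, 50 residents per home, equal SDs and no gain from matching. It grows with the ICC and shrinks as the correlation rises. No bias over randomisation and no general loss of precision is claimed.

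**What to change.** In the Cost effectiveness analysis section, state that the effect on functional health and disability used in the ratio, the plane and the acceptability curves is the baseline-adjusted difference at 6 months from the multivariate model of the Data analysis section, re-estimated in each bootstrap replicate. Keep the difference in improvement at most as a sensitivity analysis.

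The cost is one sentence and one regression per replicate; Table 1 already has the baseline scores. The downside is slightly more computing and, if home-level differences are strongly persistent, possibly no gain in precision or some loss. The gain is that the economic results rest on an effect that the trial also reports clinically.

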### Procedure

All residents from the usual care homes as well as from the intervention homes receive an invitation letter and an informed consent form two weeks before the start of the study. If the resident is not able to understand the information and/or to sign the informed consent papers a close family member will be invited to participate and provide proxy information on the outcomes.

All eligible persons who sign an informed consent are going to be visited by an interviewer of the VU medical centre for an interview on their health and resource use. Table 1 provides an over-view of the measurements.

**Table 1 T1:** Overview of outcomes and measurements in the study

Variable	Instrument	Baseline	6 months
*Primary outcome*			
a. Quality of Care	RAI-LTCF criteria	X	X
b. Quality Adjusted Life Years	Euroqol & thermometer	X	X
c. Functional health	COOP-WONCA & SF12	X	X
*Secondary outcome*			
d. Patient care satisfaction	Brief Quote on elderly Homes	X	X
e. Disability ADL-IADL	Groningen Activity Restriction Scale	X	X
f. Mood disorders	PRIME-MD	X	X
g. Hospital days	Checklist resource utilization Hospital records	X	X
h. Time to nursing home placement	Registration elderly home HIS		X
i. Time to mortality	Registration elderly home HIS		X
Economic outcomes			
Direct costs	Patient/family Interview Registration pharmacy Registration medical records		X
*Process outcomes*			
Adherence professionals to disease management protocol	Checklist		X
Adherence of patients to specific disease management recommendations	Checklist		X
Potential Effect Modifiers			
-Sociodemographics	Patient Interview	X	
-Health status (morbidity, medication)	Patient Interview Patient records	X	X
-House & personnel characteristics	Staff Interview	X	

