#### Primary outcomes are

1. Quality of care as measured with the risk adjusted criteria [27],

2. Quality Adjusted Life Years using health utilities is measured with the Euroqol [28,29],

3. Functional health is measured by COOP-WONCA charts [30,31] (Nelson 1983, Van Weel 1995) and Short Form 12 item version [32].

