#### Secondary outcome measures are

4. Care satisfaction of residents is measured by the brief QUOTE, which wording was slightly adapted to fit the institutional setting [33].

5. ADL and IADL disability is measured by GARS [34].

6. (Days until) placement in a nursing home is surveyed and crosschecked at institutes.

7. (Acute) hospitalization is surveyed and cross-checked at the local hospital which covers 95% of all admissions in the region.

8. (Days until) mortality is checked in the administration of the homes.

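### The baseline adjustment planned for the 6-month EuroQoL comparison is not extended to the QALY difference or its bootstrap, although baseline utility carries half the weight of the two-point QALY

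*Protocol article*

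**What the plan says.** All references are to the protocol article.

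- **Status of the QALY.** The list of primary outcomes includes it: "Quality Adjusted Life Years using health utilities is measured with the Euroqol".
- **Measurement points.** Table 1 (Procedure) marks two, baseline and 6 months: "Quality Adjusted Life Years Euroqol & thermometer X X".
- **Construction.** Under Cost effectiveness analysis, utility is multiplied "with the amount of time a patient spent in this particular health state", and "Transitions between health states are linearly interpolated". Uncertainty comes from a bias-corrected percentile bootstrap with 5000 replications of cost and effect pairs. No covariate is mentioned.
- **Effect analysis.** Data analysis compares the arms "at 6 months on the outcome measures (risk adjusted interRAI LTCF based Quality indicators, EuroQoL, functional health and disability". On adjustment it says: "We will use the multivariate technique to adjust for possible differences in baseline scores and background variables between the intervention and control groups". The list names EuroQoL but not the QALY.
- **Design.** Five homes are allocated to each arm, with over 500 residents in all. Homes are matched in pairs on the percentage of psychogeriatric residents.

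**The concern.** With two utility points and a straight line between them, the QALY is the average of baseline and 6-month utility times half a year. A difference between arms at baseline therefore counts as a QALY difference, through its own term and again through its correlation with 6-month utility.

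The article expects such differences. Data analysis provides for adjustment of baseline scores, and the Discussion concedes that habits of the homes will not be spread evenly over the arms. With ten randomised units, matched on a variable other than utility, chance imbalance in utility is likely. The stated protection is tied to the comparisons at 6 months. No protection is stated where the QALY is formed and bootstrapped. At stake are one of three primary outcomes and the cost-utility ratio with its acceptability curve.

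**Working it through.** **The plan's own figure.** The article gives no QALY figure to reproduce. Its planning effect for health-related quality of life, 0.5 SD, serves as the yardstick below. That calculation reproduces: a two-sided t-test at alpha 0.05 and 80% power needs 63.8, so 64 per group. Then 64 × 1.10 / 0.85 = 82.8, stated as 82.

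**Step 1: QALY formula.** With utilities u0 and u6 and 0.5 year of follow-up,

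QALY = 0.5 × (u0 + u6)/2 = 0.25·u0 + 0.25·u6.

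**Step 2: pass-through of a baseline difference.** Let d be the difference between arms in mean u0, and b the slope of u6 on u0. With no treatment effect the expected difference in u6 is b·d, so the unadjusted QALY difference shifts by 0.25·d·(1 + b). For d = 0.05 this is 0.0125 (b = 0), 0.020 (b = 0.6) or 0.025 (b = 1).

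**Step 3: size of a chance imbalance.** For m residents in each of five homes per arm,

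SE(d) = SD × √(2 × [1 + (m − 1) × ICC] / (5m)).

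The five homes per arm come from the article, and m = 50 follows from about 500 residents in ten homes. SD = 0.25, ICC = 0.01 to 0.05 and b = 0.6 are assumptions.

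- ICC 0.01: SE = 0.25 × √(2 × 1.49/250) = 0.0273. Times 0.25 × 1.6 = 0.40, this is 0.0109 QALY.
- ICC 0.05: SE = 0.25 × √(2 × 3.45/250) = 0.0415. Times 0.40, this is 0.0166 QALY.

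**Step 4: comparison with the planned effect.** An effect of 0.5 SD at 6 months is 0.125 utility, worth 0.25 × 0.125 = 0.031 QALY. A one-standard-error imbalance is thus 0.35 (ICC 0.01) to 0.53 (ICC 0.05) of it.

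For SD 0.20 to 0.30 and ICC 0 to 0.10, with 50 per home, the shift is 0.007 to 0.026 QALY and the ratio 0.29 to 0.70. With only the minimum sample (82/5 = 16.4 per home) the ratio is 0.50 to 0.80.

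**Step 5: what adjustment buys.** In 4000 simulated trials per ICC with no true effect (ten homes of 50, SD 0.25, b = 0.6, pair matching ignored):

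| ICC | SD of QALY difference, unadjusted | SD, regressed on u0 |
|---|---|---|
| 0.01 | 0.012 | 0.0045 |
| 0.05 | 0.017 | 0.0045 |
| 0.10 | 0.022 | 0.0045 |

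The slope of the estimated difference on the baseline imbalance falls from 0.40 to 0.00. In this model homes differ only through baseline utility. If they also differ in 6-month utility at a given baseline, the adjusted SD will exceed 0.0045, so the table is a favourable case for adjustment.

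**Step 6: deaths, a side point.** For a resident with assumed utility 0.6 who dies at month 1, a line to zero at month 6 gives 0.5 × 0.6/2 = 0.150 QALY. Baseline utility held to the date of death gives 0.6/12 = 0.050, and a line to zero at that date gives 0.025. The article does not say which convention applies.

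**The case against.** The strongest reply is that this is silence, not error. Linear interpolation is a sound rule. Data analysis does plan baseline adjustment with EuroQoL on its list, and Table 1 gives EuroQol as the instrument for the QALY, so EuroQoL there may simply be a label for that outcome. A condensed article may leave the cost-utility model to the full plan. SD, ICC and slope are all assumed, and matching on psychogeriatric percentage may reduce imbalance in utility.

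Much of this stands, and it rules out several stronger readings.

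- A reader might infer that the trial ignores baseline utility or will analyse raw QALYs. No section says so, and the 6-month EuroQoL comparison is adjusted.
- A reader might infer that the primary outcome was replaced by a 6-month score. The wording about 6 months points that way, but the labelling explanation is not excluded.
- A reader might infer that deaths are mishandled. The article weights utility by time spent in a state, records days until death, plans an intention-to-treat analysis and excludes residents expected to die within six months. A proper treatment of deaths is compatible with all of this, and deaths do not cause baseline imbalance in any case.
- A reader might extend the point to adjusting costs for baseline resource use. Table 1 marks direct costs at 6 months only, while the economic sections mention a baseline interview. It is therefore unsettled whether the data would exist.

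The reply does not remove the core. The adjustment is attached to comparisons at 6 months, the section that forms and bootstraps the QALY states none, and a two-point QALY is the quantity in which baseline utility matters most.

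**Conclusion.** The point holds in a limited form. Followed as written, the article protects the 6-month EuroQoL comparison against baseline imbalance but states no such protection for the QALY difference or the bootstrapped pairs. If the QALY is in fact left unadjusted, a one-standard-error chance imbalance moves it by about 0.011 to 0.017, roughly a third to a half of the 0.031 QALY that the planned effect is worth. This rests on the assumed SD, ICC, slope and 50 residents per home, and ignores the pair matching. The formula and the pass-through of 0.25·d·(1 + b) do not depend on the assumed values. This is a worthwhile improvement at no cost to a primary outcome, not proof that the analysis will be wrong. The handling of deaths is a secondary clarification only.

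**What to change.** 1. In Cost effectiveness analysis, state that the QALY difference is estimated by regression on arm and baseline utility, allowing for home, and that this is done inside each bootstrap replicate so that the cost-effect pairs use the adjusted difference.
2. In Data analysis, state that the primary-outcome analysis covers this baseline-adjusted QALY as well as the 6-month EuroQoL score.
3. As a clarification, state that QALYs are counted only up to the recorded date of death, which utility applies between baseline and death, and that residents who die stay in the analysis.

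The cost is a few sentences. Baseline EuroQol, home and date of death are already collected, and no visit, instrument or sample-size change is needed.
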